## Abstract

**Background:**

Despite overwhelming evidence of clinical benefit for patients with heart failure (HF), the uptake of guideline‐directed medical therapies (GDMT) has been slow. Collaborative approaches are critically needed to improve alignment between evidence and clinical practice. Many strategies proposed to improve GDMT implementation have been either ineffective or too resource‐intensive to implement at scale across different practice contexts. Furthermore, most existing approaches focus primarily on patients with HF and reduced EF, despite growing evidence for effective pharmacologic therapy in those with HF and mildly reduced or preserved ejection fraction (HFpEF).

**Hypothesis:**

Based on this experience, we designed the Cooperative Program for ImpLementation of Optimal Therapy in Heart Failure (COPILOT‐HF) study (NCT05734690).

**Methods:**

This is a pragmatic, randomized, open‐label intervention trial to compare a comprehensive, remote, navigator‐led, algorithm‐driven strategy for optimization of GDMT prescribing in patients with HF across the full spectrum of ejection fraction with a control intervention focused on patient and provider education regarding the importance of GDMT optimization.

**Results:**

The primary efficacy endpoint of the study is the proportion of patients receiving optimal HF treatment at 3 months. Additional outcomes of interest include the proportion of patients with optimal HF therapy at 6 months and 12 months as well as health resource utilization, including hospitalizations and deaths.

**Conclusions:**

COPILOT‐HF will evaluate the effectiveness of an early implementation of a remote pharmacist‐led medication titration strategy across the HF spectrum.

## Introduction

1

The last two decades have seen dramatic advances in the development of effective pharmacologic therapies for patients with heart failure (HF) across the full spectrum of left ventricular ejection fraction (LVEF) [1]. Current guidelines from the ACC/AHA/HFSA and from the ESC recommend treatment of all patients with symptomatic HF and reduced EF (LVEF < 50%) with a four drug regimen including an evidence‐based beta blocker (BB), an angiotensin receptor neprilysin inhibitor (ARNI) (in preference to an ACE inhibitor or ARB), mineralocorticoid receptor antagonist (MRA), and sodium‐glucose co‐transporter 2 inhibitor (SGLT2i) [2]. Although evidence‐based recommendations for patients with HF and higher EF have historically been lacking, newer data supports extension of the same four drug therapy to patients with HF and mildly reduced ejection fraction (LVEF 41%–49%), and use of SGLT2 inhibitors for patients with symptomatic HF regardless of EF (including patients with HF and mildly reduced or preserved ejection fraction [HFpEF], LVEF ≥ 50%) [3, 4]. [2, 5]. Growing endorsement by guidelines of pharmacologic treatment for HF across the full spectrum of EF heightens the urgency for clinicians to deploy these treatments in clinical practice.

Despite the evolution of guidelines based on compelling evidence from randomized clinical trials, utilization of recommended therapies remains suboptimal in clinical practice [6, 7], with implications for preventable death, disability, and healthcare‐related costs. Registry data from the US and Europe suggest that one in three eligible patients with HFrEF is missing treatment with one or more key recommended therapies, and for those who are treated, underdosing is common. Although utilization of newer therapies such as ARNI and SGLT2i might be anticipated, rates of MRA utilization as low as 30% suggest major lingering implementation gaps [6, 7]. Although registry data regarding treatment of H patients with mildly reduced or preserved EF is limited, recent clinical trials enrolling this population suggest that less than one in five eligible patients is treated with an SGLT2i [8].

Several strategies have been developed to close the implementation gap between evidence and practice for HF patients. Trials of timely alerts delivered via electronic health records (EHRs) [9], virtual inpatient care‐teams [10] to nudge providers to prescribe guideline‐directed medical therapies (GDMT), and interventions to educate patients about GDMT to impact prescriber behavior [11] have demonstrated only modest efficacy and virtually all have excluded patients with HF and LVEF > 40%, who comprise a growing proportion of the population [12]. The Safety, Tolerability and Efficacy of Rapid Optimization, Helped by NT‐proBNP Testing, of Heart Failure Therapies (STRONG‐HF) trial showed that early and rapid up‐titration of GDMT significantly reduced 180‐day all‐cause mortality and HF readmissions [13]. However, owing to its resource‐intensive protocol, the scalability of the STRONG‐HF approach within the current practice environment in the United States may be challenging. Therefore, there is a substantial need for similarly effective but scalable programs to improve guideline‐directed management of HF.

We have previously implemented a successful quality improvement program utilizing a remote, navigator‐led, pharmacist‐driven strategy to facilitate medication optimization in patients with HFrEF [14]. Following that effort, newer therapies (e.g., SGLT2i), expanded regulatory labeling (e.g., ARNI in HFpEF with low‐normal EF), and revised guideline recommendations have collectively stressed the need for renewed approaches to optimize GDMT across the HF spectrum [1, 15]. Therefore, we designed the Cooperative Program for ImpLementation of Optimal Therapy in Heart Failure (COPILOT‐HF) trial to determine whether a similar remote management approach in patients with HF across the spectrum of EF will achieve a higher rate of GDMT implementation than a strategy of patient and provider education followed by remote HF clinic management. In addition, we aimed to determine, in eligible patients with left ventricular EF < 50%, whether the sequencing of GDMT initiation (traditional vs. SGLT2i‐first) leads to improved GDMT intensification. Herein, we summarize the key design elements of this trial.

## Program Design

2

COPILOT‐HF is a pragmatic, randomized, open‐label intervention trial to investigate the comparative effectiveness of two remote care strategies on optimizing the prescription of GDMT in patients with HF (Figure 1). The first strategy is an “education‐first” approach in which the intervention is provider and patient education with the intention of improving patients' understanding of their diagnosis and its management to increase acceptance and compliance of medical therapy. At 3 months postrandomization, this is followed by a remote clinic that implements a standardized, stepped‐approach to GDMT optimization. In the second approach, provider and patient education is started simultaneously with remote GDMT management clinic. The trial is registered at: https://clinicaltrials.gov/study/NCT05734690.

**Figure 1 clc70222-fig-0001:**
[figure not shown]
Clinical trial design.

### Patient Selection and Enrollment

2.1

Recruitment and screening will be performed within the Mass General Brigham (MGB) health system which is a nonprofit, academic healthcare system serving Massachusetts and New Hampshire and encompassing a comprehensive network that includes 2 academic medical centers (Brigham and Women's Hospital [BWH] and Massachusetts General Hospital), 12 community and specialty hospitals, and extensive network of affiliated physicians, numerous community health centers, and a dedicated home care organization. Patients aged 18–90 years with an established diagnosis of HF regardless of LVEF will be included in the study. All patients will be required to (1) have an established longitudinal relationship with a primary care provider (PCP) or a cardiologist within MGB with ≥ 1 clinic visit within 2 years before enrollment, (2) have undergone a transthoracic echocardiogram (TTE) within the 2 years before enrollment, and (3) have had symptomatic HF within the 2 years before enrollment. Criteria for determining if a patient has symptomatic HF include prior HF hospitalization, regular use of loop diuretics, or documentation of symptoms attributed to HF by the PCP or cardiologist, including but not limited to dyspnea, lower extremity edema, orthopnea, or paroxysmal nocturnal dyspnea. Detailed study inclusion and exclusion criteria can be found in Table 1.

**Table 1 clc70222-tbl-0001:** Inclusion and exclusion criteria.

Inclusion criteria	Exclusion criteria
Adults aged 18–90 years Diagnosis of ACC/AHA Stage C heart failure Current HF symptoms or symptoms within the past 24 months Most recent LVEF assessed within the past 24 months Seen a Mass General Brigham Provider within the past 24 months Within the last 24 months English or Spanish speaking	LVEF < 50% currently prescribed or intolerant to an evidence‐based beta‐blocker, ARNI, MRA, and SGLT2i at least 50% goal dose LVEF ≥ 50% currently prescribed or intolerant to SGLT2i Systolic blood pressure (SBP) < 90 mmHg at last measure Current severe aortic stenosis or severe aortic insufficiency Group 1 pulmonary arterial hypertension on disease‐specific therapies (e.g., Ambrisentan, Bosentan, Epoprostenol, Treprostinil, and Iloprost) Congenital Heart Disease Established hypertrophic cardiomyopathy with or without LVOT obstruction Type 1 diabetes Established diagnosis of cardiac amyloidosis eGFR < 30 mL/min/1.73 m^2^ Active chemotherapy Receiving end‐of‐life care or hospice History of transplant, currently listed above status 4 or being evaluated for transplant Outpatient intravenous inotrope use Current use of a ventricular assist device Currently pregnant or breastfeeding Physician's discretion is inappropriate for remote management program

Potential participants for the study are identified from several sources, including the MGB enterprise data warehouse, inpatient hospitalization dashboards, direct provider referrals, and patients previously managed by the MGB Remote Health team [14]. To identify potential MGB participants likely to meet eligibility criteria, we constructed a search query using billing codes, a clinician‐curated EHR problem list, and TTE reports for LVEF groups [16]. In addition, we implemented a best practice alert (BPA) to nudge patients' PCPs, cardiologists, and inpatient teams to augment referrals for potential enrollment. We will use summary reports of BPAs triggered for hospitalized patients and contact them postdischarge if they are eligible.

A study staff member verifies patients' eligibility. Through email or in‐basket messaging via the EHR, the program notifies potential participants' providers (cardiologists and PCPs) of the program details, their patient's eligibility, and the program's intent to invite their patient to participate. If a provider communicates that a patient is not suitable for the program, the program does not approach the patient. Eligible patients whose providers do not object are invited to participate through a secure patient gateway message. Potential participants who respond to neither the personalized letter nor the email research invitations are contacted by phone. Patients interested in participating are sent the electronic informed consent form (eConsent) via REDCap. Each patient's preferred method of communication will also be solicited and recorded by the study team. This protocol was approved by the MGB Human Research Committee.

Enrollment for the COPILOT‐HF trial has been completed. We anticipate completing follow‐up for all participants and reporting results by January 2026.

### Randomization

2.2

Once a patient agrees to participate in the program, they are randomized in a 1:1 manner at the patient level into either (1) the “education‐first” arm (3‐month period of patient and provider education, followed by enrollment in a remote HF medication management program for the optimization of GDMT) or (2) the “simultaneous” arm (parallel participation in patient and provider education and enrollment in a remote HF medication management program for the optimization of GDMT). Education consists of curated print and video microlearning content for patients and providers' notification regarding their eligibility for GDMT before active participation in the remote management GDMT clinic. For patients enrolled with LVEF < 50% not on SGLT2i at baseline, we will perform a secondary randomization to test a strategy of medication titration sequencing using SGLT2i first versus traditional titration sequencing. Traditional titration sequencing is based on approval dates of medications and guideline sequencing and follows the order of BB, ARNI/ACEi/ARB, MRA, and SGLT2i. Patients will be stratified by LVEF (≥ 50% and < 50%) and by enrollment category, either outpatient or post‐hospital discharge (defined as within 30 days of discharge) for prespecified secondary analysis. All randomizations will be completed through computer‐generated algorithms using block randomization with block sizes of 30 without stratifying based on LVEF to ensure an equal number of patients in each group. The randomization allocation based on the blocks will be concealed to the study personnel.

### Intervention

2.3

While the patients are enrolled in the remote GDMT optimization program, medication titration is managed under a Collaborative Drug Therapy Management (CDTM) agreement by a pharmacist. A team including pharmacists, advanced practice providers, general cardiologists, and HF specialists developed a medication management algorithm. The algorithm includes initiation, titration, and discontinuation of BB, ARNI, angiotensin converting enzyme inhibitors, angiotensin II receptor blockers, MRA, and SGLT2i based on LVEF categories (Figure 2). Since guidelines for HFpEF incorporating new study data have not been formally published in the United States at the time of study initiation, algorithms were created based on expert consensus documents [17, 18] as well as recent updates to ESC guidelines. Following the same expert consensus documents [17, 18], we set the LVEF threshold for HFpEF as ³50% and added ARNI and MRA to the treatment algorithm for those with an EF 50–59% based on the extended benefits of MRAs and ARNIs in “less‐than‐normal” LVEF [17]. Consequently, the final medication initiation and titration protocol included LVEF categories of < 50%, 50%–59%, and ≥ 60%. These management plans were approved by the BWH Pharmacy and Therapeutics Committee.

**Figure 2 clc70222-fig-0002:**
[figure not shown]
Medication titration algorithm. (A) Medication algorithm for HFrEF, (B) Medication algorithm for HFpEF; SGLT2i (sodium glucose cotransporter‐2 inhibitor), MRA (mineralocorticoid receptor antagonist), ARNI (angiotensin receptor‐neprilysin inhibitor), ACEi (angiotensin‐converting enzyme inhibitor), ARB (angiotensin II receptor blocker), MTD (maximum tolerated dose).

We constructed a customer relationship management platform using Microsoft Dynamics 365 [19], which enables automated data integration from the EHR and medication management with follow‐up by a multidisciplinary team. All aspects of the platform comply with the Health Insurance Portability and Accountability Act of 1996 and institutional requirements.

Navigators, a group of nonclinicians specifically trained to approach patients for the purposes of this study, are primarily responsible for communicating with prospective and enrolled participants. Titration of GDMT is performed by a team of navigators and pharmacists supervised by an advanced practice practitioner (APP) and a cardiologist. Based on a predetermined algorithm, successive medication adjustments are determined by a clinical pharmacist and relayed to the navigator. Navigators communicate with program participants via phone for medication adjustments and monitoring of adverse events, blood pressure, and laboratory values. If the patient accepts the proposed medication adjustment, navigators relay this information to the pharmacist, who sends the new prescription to the patient's preferred pharmacy. Cost, side‐effects, hypotension, and/or laboratory changes as barriers to medication class or dose optimization will be collected at the time of medication initiation attempt. If a patient cannot afford a medication, the study team performs prior authorizations, tier exemptions, and referrals to Serving the Health Insurance Needs of Everyone councilors to assist Medicare‐eligible patients in overcoming financial barriers. The study team also aids participants with Patient Assistance Program applications which are income‐based programs help provide access to medication at low or no cost to the patient, or assists patients in signing up for copay cards to increase medication access. If cost limitations persist, this will be documented and communicated to the patient's primary care and/or cardiology team in the EHR. Patients are able to decline suggested GDMT adjustments for any reason, and this will be documented if it occurs. Specific rules governing sequencing and titration of each medication class are provided in Figure 2.

Educational videos, including information regarding HF diagnosis, HF medications, and self‐care for HF, are shared with program participants on a patient engagement and education platform (Mytonomy) without need for registration. For patients with limited access to electronic devices or who are otherwise unable to access the videos, we will send printed educational material that covers the same topics as the educational videos. Providers are sent a message detailing the LVEF group of their patient with an attached medication algorithm that they are recommended to follow.

### Outcomes and Follow‐Up

2.4

The primary endpoint of the study is the percent of eligible enrolled patients who achieve utilization of recommended pharmacotherapy for HF at 3 months after randomization, which includes (1) prescription utilization of all four drug classes (ARNI/ARB/ACEI, SGLT2i, BB, and MRA) at any dose in patients with LVEF < 50% and (2) prescription of SGLT2i in patients with LVEF ≥ 50%. This binary primary endpoint was chosen for its pragmatic simplicity, applicability across both HFrEF and HFpEF populations, and alignment with current guideline‐directed treatment goals. It offers a clear and clinically meaningful measure of successful implementation of foundational therapy that can be consistently interpreted across HF phenotypes. The prespecified primary, secondary, and exploratory outcomes are summarized in Table 2.

**Table 2 clc70222-tbl-0002:** Study endpoints and outcome measures.

Endpoint category	Specific measure	Definition/details	Time point of assessment (months)
Primary endpoint	Utilization of recommended therapy	Percent of eligible patients achieving: LVEF < 50%: Utilization of four GDMT classes (ARNI/ARB/ACEI, SGLT2i, BB, and MRA). LVEF ≥ 50%: Utilization of an SGLT2i.	3
Secondary endpoint	Any intensification of GDMT	Any initiation or dose titration of a GDMT medication.	6
**Other efficacy and safety endpoints**			
Process metrics	Number of new GDMT medication classes added	Absolute count of new classes initiated.	6
	Percent reaching maximum tolerated dose	Proportion of patients at maximum tolerated dose for each GDMT class.	6
	Percent on ≥ 50% recommended dose	Proportion of patients on at least 50% of the recommended target dose for each class.	6
	Prescription for four optimal‐dose classes	Proportion of patients with LVEF < 50% who have a prescription for all four GDMT classes at optimal dose.	6
	Utilization of four optimal‐dose classes	Proportion of patients with LVEF < 50% with self‐reported utilization of all four GDMT classes at optimal dose.	6
	Prescription for SGLT2i	Proportion of patients with LVEF ≥ 50% with a prescription for an SGLT2i.	6
	Utilization of SGLT2i	Proportion of patients with LVEF ≥ 50% with self‐reported utilization of an SGLT2i.	6
	Prescription for ARNI/MRA/SGLT2i	Proportion of patients with LVEF 50%–59% with a prescription for ARNI, MRA, and SGLT2i.	6
	Utilization of ARNI/MRA/SGLT2i	Proportion of patients with LVEF 50%–59% with self‐reported utilization of ARNI, MRA, and SGLT2i.	6
	Any worsening HF	Composite of worsening NYHA functional class or hospitalization for HF.	6
Surrogate clinical outcomes	Weight change	Change from baseline (kg).	6
	Blood pressure	Change from baseline (mmHg).	6
	NT‐proBNP	Change from baseline (pg/mL).	6
Clinical outcomes (efficacy and safety)	Any worsening HF	Composite of worsening NYHA functional class or hospitalization for HF.	6
	Hypotension	Systolic blood pressure < 90 mmHg with associated symptoms.	6
	Hypo/hyperkalemia	Serum potassium < 3.0 mmol/L or > 6.0 mmol/L.	6
	Acute kidney injury (AKI)	Increase in serum creatinine by ≥ 1.5 times the baseline value.	6
	Any hospitalization	All‐cause hospitalization.	6
	Death	All‐cause mortality.	6
Health utilization outcomes	Emergency department visit	All‐cause and HF‐specific.	6
	Hospital admission	All‐cause and HF‐specific.	6
	*Patient & provider‐reported outcomes*		
	Patient satisfaction	Net promoter score (NPS) survey.	6
	Provider satisfaction	Assessed via survey.	6
Exploratory outcomes	GDMT medication prescriptions	Analysis of prescription patterns at multiple time points.	1, 2, 6, and 12
	Cost‐effectiveness analysis	Economic analysis of the intervention.	12
	Heart failure collaboratory GDMT score	Change from baseline (for patients with LVEF < 50%).	6
	Optimization potential score	Change from baseline (for patients with LVEF < 50%).	6

Abbreviations: ACEI, angiotensin‐converting enzyme inhibitor; AKI, acute kidney injury; ARB, angiotensin II receptor blocker; ARNI, angiotensin receptor‐neprilysin inhibitor; BB, beta‐blocker; GDMT, guideline‐directed medical therapy; HF, heart failure; LVEF, left ventricular ejection fraction; MRA, mineralocorticoid receptor antagonist; NPS, Net Promoter Score; NT‐proBNP, N‐terminal pro‐B‐type natriuretic peptide; NYHA, New York Heart Association; SGLT2i, sodium‐glucose cotransporter‐2 inhibitor.

The secondary endpoint is any intensification of GDMT at 3 months, which includes any initiation or titration of a GDMT medication. Intensification of GDMT, which includes any initiation or titration of a GDMT medication, will be captured as the number of intensification steps and compared between treatment groups. For example, the initiation of any dose of an ACEi, followed by two titrations and the initiation of SGLT2i, would count as four intensification steps. We will then compare the primary and secondary outcomes between groups at 6 months postenrollment after all patients receive the remote HF clinic intervention. Patients will be followed actively for 6 months or to the end of active medication management; however, we will continue to obtain data from EHR for another 6 months and compare outcomes at 12 months postenrollment to assess the durability of the results. An interim analysis will be performed after 100 participants have completed 4 months of the program to assess if any changes to the study design are needed based on efficacy, safety, and operational metrics.

The primary analyses will be performed according to the intention‐to‐treat principle, using data for all randomized patients. The “education‐first” group will be compared with the “simultaneous” medication titration and education groups. Sensitivity analyses will be performed in patients engaged in the program for at least 3 months, and in patients who complete the treatment program.

For the second randomization in participants with HFrEF comparing different sequencing of therapies, we will analyze primary and secondary outcomes by comparing patients in the “SGLT2i‐first” and “traditional pathway” GDMT sequencing groups.

Other efficacy and safety endpoints will include incidence of emergency department visits, hospitalizations, and deaths adjudicated as attributable to adverse drug reactions within our protocols, during study follow‐up in both groups. We will explore the barriers to the initiation or continuation of GDMT, including, but not limited to, cost, adverse events, provider medication changes, and patient compliance and preferences. We will also perform additional analyses for process metrics, surrogate outcomes (weight change, blood pressure, and NT‐proBNP level), traditional clinical outcomes (worsening HF, hospitalization for HF, all‐cause hospitalization, and death), healthcare utilization, and patient satisfaction.

Finally, we will perform prespecified analysis across various subgroups of interest, including age, sex, race, ethnicity, primary insurance, comorbid conditions, type/setting of enrollment (outpatient vs. post‐HF hospitalization), and baseline LVEF.

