### Statistical Plan

2.5

We estimate that the baseline percentage of patients with HF who meet the primary endpoint definition will be ~10% [11]. In the education/notification arm, we anticipate a ~4% absolute improvement to ~14% based on other studies with educational interventions that target patients [11]. Based on our previous experience, we hypothesize that a strategy of a remote, navigator‐led, pharmacist‐driven HF program will increase this proportion to 25% at 3 months after randomization. Our prior pilot study of a similar remote, navigator‐led program formed the basis for this estimate [14]. With 250 patients in each strategy group (500 patients in total) there will be > 85% power to detect a significant difference between groups at a two‐sided 0.05 significance level. We estimate a rate of dropout (patients who stop receiving treatment from the program) of 10%. The primary endpoint (as determined by last observed medication use) will be assessed in all patients.

For the second randomization of the sequence of GDMT therapy initiations in patients with LVEF < 50%, we expect that the percentage of patients in the traditional titration sequencing group who meet the primary endpoint will be 15%. Considering an imbalanced enrollment of patients with HFrEF and HFpEF, with 40% of patients with HFrEF, a total of 100 patients in each group will provide 80% power to detect an 18% difference between groups at a two‐sided 0.05 significance level, with an estimated 10% dropout (patients who stop receiving treatment from the program). This assumption is supported by prior real‐world data demonstrating hyperkalemia rates of approximately 28%–38% with traditional GDMT sequencing, as well as clinical trial data showing that SGLT2 inhibitors reduce the incidence of hyperkalemia and hypotension [20, 21, 22] —two common barriers to the initiation and up‐titration of MRAs and ARNIs [23, 24]. Based on these findings, we believe that initiating therapy with an SGLT2i may mitigate these adverse effects and lead to a higher proportion of patients achieving full GDMT in this arm.

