The roll over from education‐first to simultaneous education and medication management at 3 months in a clinical trial of HF is an important aspect of the trial design. The “education‐first” allows for an “enhanced standard of care” with notification of both patients and providers of their eligibility for these medication classes—and education to both patient and provider of the rationale for these recommendations. By allowing patients to roll over to the medication management arm, both providers and patients will not be left without appropriate prescriptions for guideline‐directed medical therapy even if these are not prescribed by their regular care team. It will allow for a period of randomized comparison between groups. HF patients may benefit from an incremental approach to treatment, especially if they are not acutely ill. Starting with education allows patients to gain knowledge about their condition and the importance of adherence to treatment regimens. After this initial period, introducing medication management gradually may help patients better understand and accept the necessity of their medications. This phased approach might enhance patient engagement and long‐term adherence. The roll over at 3 months allows for an assessment of the safety and tolerability of medications, particularly if patients in the education‐first arm are not already on these medications. This analysis can inform decisions about the most effective treatment approach. The analysis at 6 months will assess for the ability of the education‐first group to demonstrate any effects of education pre‐treatment on treatment uptake or adherence to therapy. This period, with enough time to complete full titration with multiple months of buffer, will assess for any differences in uptake or adherence to therapy at what would be a steady state after the initiation and titration period for both groups. Many of the traditional medications used for the treatment of HFrEF can cause hypotension—often limiting further initial titration of GDMT—or hyperkalemia, which also often causes a slowdown or cessation of attempts by providers to continue with GDMT initiation and titrations. By starting therapy with an SGLT2i—a class of medications known to have little effect on blood pressure, as well as a mild reduction in serum potassium, we believe that starting with SGLT2i may mitigate both hyperkalemia and hypotension‐related treatment gaps.

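### The single potassium safety endpoint merges low and high values, so it is poorly suited to show the fall in hyperkalemia that the plan cites for the sequencing randomization

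*Protocol article*

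**What the plan says.** - **Endpoint.** Section 2.4, Table 2, lists a single hypo/hyperkalemia row among the clinical efficacy and safety outcomes, assessed at 6 months: "Serum potassium < 3.0 mmol/L or > 6.0 mmol/L". No row covers hyperkalemia alone, hypokalemia alone or change in potassium. Symptomatic hypotension has its own row.
- **Rationale.** Section 2.5 supports the assumed sequencing difference with "hyperkalemia rates of approximately 28%–38% with traditional GDMT sequencing" and with trial data that "SGLT2 inhibitors reduce the incidence of hyperkalemia and hypotension". It concludes that starting with an SGLT2i "may mitigate these adverse effects and lead to a higher proportion of patients achieving full GDMT in this arm". The Discussion repeats the argument and describes the class as having little effect on blood pressure "as well as a mild reduction in serum potassium".
- **Sequencing comparison.** Section 2.4 says of the second randomization that "we will analyze primary and secondary outcomes by comparing patients in the" two sequencing groups. Potassium and hypotension are neither primary nor secondary; Table 2 places them under other efficacy and safety endpoints.
- **Sizing.** Section 2.5 sizes this comparison on the primary endpoint: 15% in the traditional group, an 18-point difference, 100 per group, 80% power, 10% dropout.

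**The concern.** An endpoint met by either of two opposite events works poorly when the treatment is expected to shift the underlying variable in one direction. On the plan's own account, SGLT2i-first lowers potassium. That should give fewer values above 6.0 and, if it affects low values at all, more below 3.0. The pooled count then nets a benefit against a harm.

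Two things are at stake. One is explanation: if SGLT2i-first wins or loses on full GDMT, the reader will want to know whether hyperkalemia differed, and the pooled row is a weak guide. The other is safety reporting: a pooled count does not say which harm occurred. This applies to the main strategy comparison too, because the remote clinic starts both drugs that the Discussion says can raise potassium and a class that it says lowers it.

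**Working it through.** **1. The plan's own figure.** Inputs from Section 2.5: p1 = 0.15, p2 = 0.15 + 0.18 = 0.33, two-sided 0.05, 80% power, 10% dropout. With mean proportion p̄ = 0.24,

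n = [1.960 × √(2 × 0.24 × 0.76) + 0.842 × √(0.15 × 0.85 + 0.33 × 0.67)]² / 0.18² ≈ 87.2, so 88 per group.

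Allowing for dropout, 88 / 0.90 = 97.8, so 98 against the stated 100. Power is 81.3% with 90 evaluable per group and 85.2% with 100. The stated size reproduces, and no potassium figure enters it.

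**2. What pooling does.** Let H be the proportion with a value above 6.0 and L the proportion with a value below 3.0, and assume no patient has both. The pooled difference, traditional minus SGLT2i-first, is

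(H_trad − H_SGLT2i) − (L_SGLT2i − L_trad).

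The document gives neither H nor L, so every rate below is an assumption. H is halved from 5% to 2.5% throughout.

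| Low values, traditional vs SGLT2i-first | Pooled proportions | Pooled risk ratio |
|---|---|---|
| none counted (hyperkalemia alone) | 5% vs 2.5% | 0.50 |
| 1% vs 1% | 6% vs 3.5% | 0.58 |
| 3% vs 3% | 8% vs 5.5% | 0.69 |
| 1% vs 3.5% | 6% vs 6% | 1.00 |

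Rows two and three show dilution, and the last shows full offset. The last row was chosen to demonstrate that offset is possible, not that it is likely.

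**3. Power at these rates.** Two-proportion normal approximation, two-sided 0.05, 100 per group:

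power = Φ{[|p1 − p2|√n − 1.960√(2p̄(1 − p̄))] / √(p1(1 − p1) + p2(1 − p2))}.

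- Hyperkalemia alone, 5% vs 2.5%: (0.25 − 0.527) / 0.268 = −1.03, so 15%.
- Pooled with 1% low values in each group: 13%. With 3%: 10%.
- Control rates above 6.0 from 1% to 10%, halved: about 6% to 27% for hyperkalemia alone, and about 4% to 24% when pooled with equal low-value rates of 1% to 3%.

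The approximation is rough at such small counts. Two things are clear from it. Pooling costs something even when low values do not differ between groups. And a split row remains far from powered: at 5%, detecting a halving with 80% power would need 906 per group.

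**4. The rate in the rationale.** At a control rate of 28% or 38%, a halving would have 68% or 85% power with 100 per group (64% or 81% with 90). The document does not give the potassium definition behind those rates. It therefore cannot be said how much of the 28%–38% the 6.0 cut-off would capture, only that endpoint and rationale have not been tied together.

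**The case against.** **Pooling may not be intended.** Table 2 uses the word composite where it means one, as for worsening HF, and elsewhere puts two measures in one row (all-cause and HF-specific visits). The potassium row could be shorthand for two events, with separate tabulation left to the full protocol or analysis plan. This is possible. But the definition joins the two conditions with an *or*, which describes one event, and nothing else in the article separates them.

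**The sequencing test does not depend on this endpoint.** This stands. A reader might infer that the comparison was sized on hyperkalemia; it was sized on full GDMT attainment, and hyperkalemia only supports the plausibility of the assumed difference.

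**The mechanism is not wholly unmeasured.** This also stands. Hypotension, the other half of the rationale, has its own row. Section 2.3 records hypotension and laboratory changes as barriers when a drug is started, and Section 2.4 plans to explore barriers. However, the laboratory category as described does not separate potassium from other results or high from low, and the exploration is not tied to sequencing group.

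**Silence is not exclusion.** A reader might infer that potassium and hypotension will not be compared by sequence. The text names primary and secondary outcomes but does not say *only*, so that reading is not established.

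**Splitting will not create power.** Correct, as the working shows. The gain is a count that can be interpreted.

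**Conclusion.** The point holds as a defect in one stated endpoint definition. Followed as written, the count merges two harms that the plan's own rationale would move in opposite directions. It can understate or conceal a difference in either, and it is poorly suited to show the expected fall in hyperkalemia.

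Two stronger readings are not supported. The endpoint is not incapable of showing a reduction: fewer values above 6.0 would still lower the count, and the components could be reported apart. Nor can the 6.0 cut-off be called inconsistent with the 28%–38% rate, because the article gives neither the definition behind that rate nor any rate above 6.0. For the same reason the size of the loss is unknown. The illustrations rest on assumed rates and show what is possible.

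The sequencing hypothesis, its sample size and its test are not affected. The consequence is limited to safety reporting and to explaining the sequencing result.

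**What to change.** 1. In Table 2, replace the single row with two endpoints at the cut-offs already stated: hyperkalemia (above 6.0 mmol/L) and hypokalemia (below 3.0 mmol/L).
2. In Section 2.4, where the sequencing comparison is described, name hyperkalemia, hypokalemia and symptomatic hypotension as exploratory safety outcomes compared between SGLT2i-first and traditional sequencing.
3. In Section 2.5, state the hyperkalemia definition behind the 28%–38% rate, so that rationale and endpoint can be reconciled. No threshold is proposed here, and no treatment rule changes.

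The cost is small. Blood pressure and laboratory values are already monitored (Section 2.3), and the plan already treats its secondary analyses as exploratory without multiplicity adjustment, so a few more rows fit that framework. Enrollment is complete and the trial is open-label, so the change should be documented and dated before the data are analyzed.
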